### Instrument development

All instruments were designed through an iterative process in which team members from the U.S. and Nepal collaborated to provide feedback and make revisions. Each instrument underwent multiple rounds of revisions until all team members concluded the items appropriately reflected the study’s objectives, well-developed theory and literature, and cultural context. Each instrument was translated from English to Nepali by a team member to ensure that questions would be understandable to participants without compromising construct validity.

All instruments will undergo a final round of revisions during the pre-testing phase during which time we will assess the instruments for flow, cultural appropriateness, and use of technical terms and jargon. Data collectors will provide feedback from their experiences which will be incorporated into final revisions for the instruments.

### Consent process

Prior to collection of any data, participants will be read aloud and provided an information sheet detailing the purpose of the study, expected duration of participation, types of questions they may be asked, and their options to decline to participate or quit at any time. For interview and survey participants, consent will be obtained immediately following recruitment at the individual’s home or place of work in a private space. Data collection will then immediately follow. For focus group discussions, written consent will be obtained individually at the location of data collection. When each participant arrives at the pre-determined location (shared during recruitment), the facilitator will pull them aside to a private spot, review the information and consent form, and obtain consent. The focus group discussion will not begin until individual consent has been provided by all in attendance. Consent will be received with a written signature. All participants will receive an un-signed copy of the information and consent form. Informed consent materials are available as
*Extended data* (
[name], 2020).

## Data analysis

### Qualitative

As data are being collected, researchers will use an audio recording device and will document field notes using a handheld tablet to capture the overall picture of the interview or focus group. In their field notes, hey will note their perceptions of the participant’s attitude and willingness to engage, as well as the surroundings, interruptions, or other notable characteristics of the session. Following data collection, team members will transcribe the audio recordings and translate them from Nepali to English. Researchers will omit any personally identifiable information shared in interviews and focus groups in the transcripts.

Following
Braun & Clarke’s (2006) guidelines, we will adopt an iterative, thematic analysis approach to analyze the in-depth interviews, key informant interviews, and focus group discussions to uncover prominent themes. This approach will allow us to thematize both the supply-side (e.g., clinic environments, providers’ communication patterns) and demand-side (e.g., attitudes, physical access, etc.) facilitators and barriers of immunization behaviors (
Braun & Clarke, 2006).

Researchers with experience in qualitative analysis will independently read through transcripts to gain familiarity with the data and develop an initial codebook. The team will then code transcripts independently, using QSR International's NVivo software, meeting regularly to revise the codebook as themes emerge. Codes will be added both deductively, based on our research question, and inductively as new trends appear. Team members will each be paired with another teammate, rotating on a weekly schedule, to compare codes, discuss discrepancies, and reach consensus. All transcripts will be coded by at least two team members. We will determine prominent themes by comparing codes across the in-depth interviews, key informant interviews, and focus group discussions; running word queries; and creating visual conceptual maps to link patterns.

### Quantitative

The primary objective of the quantitative analysis is to determine whether the Rejoice Architecture intervention results in greater vaccination uptake (or intentions for vaccination) among mothers (or prospective mothers) in the treatment, compared to the control, arm. Hierarchical linear regressions (HLM) will be used to test the primary hypothesis that vaccination rates (number of newborns vaccinated divided by total live births within a catchment area) in the treatment group will be significantly greater (goal is 10 percent) than that in the control group. This analysis will take into account the clustered nature of data within each of the six catchment areas (three in treatment and three in control areas).

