## Introduction

 Communicable diseases constitute a global health threat, with low- and middle-income countries experiencing the greatest burden (
The World Medical Association, 2020). Each year, 1.5 million people die from vaccine-preventable diseases, 600,000 of whom are children under the age of 5 (
Gavi, 2020). Immunization is an effective way to prevent disease and save lives, with two to three million lives saved by vaccines every year (
World Health Organization, 2019). Individuals benefit from immunization through illness prevention, reduced healthcare costs, and greater productivity for themselves and their caregivers (
Gavi, 2020;
Njau & Cairns, 2016;
Ozawa *et al.,* 2012). Children, who are often at greater risk of morbidity and mortality from communicable disease, experience greater cognitive ability, physical strength, and school performance when they receive vaccines (
Gavi, 2020;
Nandi & Shet, 2020). Immunizations also contribute to improved community health through herd immunity and greater economic stability from long-term cost savings (
Fox *et al.,* 1971;
Gavi, 2020;
Ozawa *et al.,* 2012;
Ozawa *et al.,* 2017). 

Currently, nearly 20 million children worldwide younger than one year old have not received the minimum basic vaccines they need to live long, healthy lives; 77% of which represent children living in Gavi-supported countries (
Gavi, 2020). Furthermore, only 17% of children under 1 have received the full dosage recommended by the World Health Organization (
Gavi, 2020). This coverage gap is present in Nepal, where only 78% of children between 1–2 years have received all recommended vaccines (
Ministry of Health Nepal *et al.,* 2017). It is important to note, though, that while the majority of children receive their vaccines by the age of 2, only 43% receive them at the age-appropriate times for which they are scheduled (
Ministry of Health Nepal *et al.,* 2017). Moreover, immunization coverage is highly variable in Nepal, with rates ranging from 65% in some provinces to 93% in others (
Ministry of Health Nepal *et al.,* 2017). Coverage is dependent on the specific vaccine as well, ranging from 73% for the first dose of the Pneumococcal vaccine to 98% for the Bacille Calmette Guerin (BCG) vaccine (
Ministry of Health Nepal *et al.,* 2017). These data demonstrate a critical need to ensure consistent and comprehensive coverage of immunization, including in Nepal.

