### Facilitators and barriers of immunization

Studies in Nepal show that institutional delivery is a prominent facilitator of vaccine uptake (
Acharya *et al.,* 2019;
Shrestha *et al.,* 2016).
Shrestha *et al.* (2016) offer one potential reason for this, stating that the first vaccine (BCG) is often administered immediately after birth, which is more likely to be readily available in a health facility setting than at home. Furthermore, in institutions, new mothers are surrounded by numerous healthcare staff who can share their recommendations for future vaccines (
Shrestha *et al.,* 2016).

Multiple studies in Asia and Africa have found a positive association between parental knowledge of immunization and vaccine uptake (
Odusanya *et al.,* 2008;
Owino *et al.,* 2009;
Perry *et al.,* 2020). This can refer to knowledge about the purpose of vaccines, appropriate ages to receive specific vaccines, age at which a child should complete the vaccines, and symptoms of vaccines, among other topics (
Odusanya *et al.,* 2008). Some studies show that even in areas of low literacy, parental knowledge is a significant determinant of full immunization (
Matsumura *et al.,* 2005;
Odusanya *et al.,* 2008). An important aspect of parental knowledge is awareness of the vaccine schedule, which is also strongly correlated with immunization coverage (
Owino *et al.,* 2009;
Shrestha *et al.,* 2016). In Nepal, full immunization requires seven separate visits over 15 months; it is essential that parents know and remember this schedule in order to bring their children to the facility at the appropriate time (
Acharya *et al.,* 2019).

For countries like Nepal that rely on immunization cards to track children’s vaccine records, immunization card retention is a major facilitator of uptake (
Acharya *et al.,* 2019;
Perry *et al.,* 2020).
Perry *et al.* (2020) found that in Bangladesh where, like Nepal, immunization cards are required to receive vaccines, parents are met with anger, shouting, and in some cases a fee when they lose or forget their card. Improving immunization card retention has serious implications for encouraging immunization in Nepal, where the retention rate for immunization cards is only 52% (
Acharya *et al.,* 2019).

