### Instruments

Baseline and end-line surveys will measure primary outcomes of immunization behavior and intent to immunize future children. A secondary outcome of general service utilization will also be measured. To assess influencing variables, surveys will measure vaccine knowledge, vaccine attitudes and beliefs, self-efficacy, information sources, and perceived social norms regarding immunization. To understand participants’ experiences and perceptions of their health facilities, surveys will measure quality of communication with providers, past experiences with pregnancy and delivery, and perceptions of their facility’s physical environment. Lastly, the surveys will measure concepts relating to the individual, including their demographics, common methods of communication, interspousal relationships (if married), and mental health. End-line surveys will include all items from the baseline surveys plus an additional section to measure exposure to the intervention.

Surveys will vary slightly depending on the participant’s classification. For instance, mothers of children younger than 2 will receive a survey which includes questions about their immunization behaviors. Conversely, pregnant women and prospective mothers will receive a similar survey that, instead, includes questions about their intentions to immunize their future children and, for some items, requests they answer as if they currently have a child younger than 2. All other survey items will be identical for participants, regardless of their classification.

The Health Facility Checklist will measure the quality of the interior physical environment, exterior physical environment, consultation room, storage and supplies, and accessibility of health facilities. Immunization centers are significantly smaller than health facilities and are only used once per month to provide vaccines. Therefore, the Immunization Center Checklist has been modified to measure the same concepts with only the relevant items. Both checklists use items adapted from the Rapid Assessment Tool (
Scholz *et al.,* 2015) and the Site Assessment for Inpatient Postpartum Care (
JHPIEGO, 2004).

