### Outcomes

***Immunization behavior and intent.*** Items measuring immunization behavior and intent are adapted from the Nepal Woman Questionnaire from the 2016 Demographic and Health Survey (DHS) and reflect either the degree to which participants have followed the National Immunization Schedule of Nepal (for mothers) or their intent to follow the schedule in the future (for pregnant women and prospective mothers;
Ministry of Health and Population, 2020;
Ministry of Health Nepal *et al.,* 2017).

***General service use.*** Items measuring health service utilization will address how often the participant has visited their health facility in the last three months for common health issues including family planning, pregnancy checkups, Tuberculosis treatment, diarrhea treatment, pneumonia treatment, and child sick visits.

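### The primary hypothesis is set on a catchment birth ratio that contradicts the survey-based primary outcomes and has no named data source; the survey outcome that could replace it has about 72% power, not 80%

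*Protocol article*

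**What the plan says.** The Instruments section under Quantitative methods names the primary outcomes: "Baseline and end-line surveys will measure primary outcomes of immunization behavior and intent to immunize future children". The Outcomes section says that the items "reflect either the degree to which participants have followed the National Immunization Schedule of Nepal (for mothers) or their intent to follow" the schedule later, the second part applying to pregnant women and prospective mothers. The split follows the questionnaires: "mothers of children younger than 2 will receive a survey which includes questions about their immunization behaviors", while the other two cohorts get a version that "includes questions about their intentions to immunize their future children".

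The Quantitative part of Data analysis first gives the objective as greater uptake, or intention, among mothers or prospective mothers. Its next sentence sets the primary hypothesis on "vaccination rates (number of newborns vaccinated divided by total live births within a catchment area) in the treatment group will be significantly greater" than in control, with a goal of 10 percent. A hierarchical linear regression is to allow for clustering in six catchment areas, three per arm.

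The Sampling section plans for 83% versus 93%, alpha 0.05, 80% power, six clusters and an intraclass correlation of 0.01. This gives 380 per arm, raised to 475 per arm (950 in all) for 20% attrition. Table 2 fills each arm with 150 women with a child under 1 year, 150 with a child of 1–2 years, 50 pregnant women and 125 prospective mothers.

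**The concern.** The ratio in the analysis section differs from the stated primary outcomes in four respects:

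- **Numerator:** newborns, against children under 2.
- **Denominator:** all live births in an area, against sampled women.
- **Unit:** catchment, against woman or child.
- **Construct:** vaccinated, against adherence to a schedule or intent.

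It also departs from the objective stated one sentence before it.

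An analyst who follows the hypothesis literally has no described data set to use. One who follows the outcome sections has two primary outcomes, measured in different women. At end-line, adherence, intent or a ratio from some later source could each be presented as primary. The sample size counts all four cohorts as if each woman supplied the same yes/no outcome, so the stated power belongs to none of these versions.

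**Working it through.** **1. Data sources.** The quantitative methods describe two sources. One is a two-wave survey of women aged 18 or older living within 1 km of a facility, recruited from randomly selected houses. The other is a set of baseline checklists of physical conditions. Neither counts births or vaccinated newborns in a catchment. Community volunteers keep lists of families with newborns and the child's immunization status (Sampling, under Qualitative methods), but both Sampling sections use the volunteers only to find participants.

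**2. The plan's own sample size.** Inputs: 83% and 93%, ICC 0.01, three clusters per arm, alpha 0.05 (two-sided assumed, as the article does not say), 80% power.

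- Individual-level size with pooled variance: [1.96·√(2·0.88·0.12) + 0.8416·√(0.83·0.17 + 0.93·0.07)]² / 0.10² = 164.6, so 165 per arm.
- Cluster size 380/3 = 126.7; design effect 1 + 125.7 × 0.01 = 2.257.
- 165 × 2.257 = 372 per arm, within about 2% of the stated 380.
- 380/0.8 = 475 per arm, 950 in all.

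The plan's figure is reproduced. It treats every woman as one binary observation.

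**3. Power by who supplies the outcome.** For n per arm at end-line: DE = 1 + (n/3 − 1) × 0.01; SE = √[(0.1411 + 0.0651) × DE / n]; signal = 0.10/SE. Normal power is Φ(signal − 1.96). The t version uses a noncentral t with 6 − 2 = 4 df.

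| Outcome supplied by | n per arm | DE | SE | Signal | Normal | t, 4 df |
|---|---|---|---|---|---|---|
| All four cohorts (as planned) | 380 | 2.257 | 0.0350 | 2.86 | 82% | 58% |
| Mothers of children under 2 | 300 × 0.8 = 240 | 1.790 | 0.0392 | 2.55 | 72% | 49% |
| Women pregnant at baseline | 50 × 0.8 = 40 | 1.123 | 0.0761 | 1.31 | 26% | 17% |

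With pooled variance under the null, the normal figures are 81%, 71% and 25%.

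**4. Why newborns in the panel are few.** Table 2 has 600 of 950 women with a child already born at baseline. The article reports baseline complete and the intervention still to start. With end-line about eight months after baseline, children under 1 year at baseline will be about 8–20 months old. Births after baseline therefore come mainly from the pregnant cohort. The Instruments section gives that cohort intention items, not behavior items.

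**The case against.** The best defence is that the parenthesis is a loose gloss. A rate is the mean of individual yes/no data, the same paragraph allows for clustering within catchments, and the sample size is built on individual proportions with the same 10-point goal. The authors may well have meant an individual survey outcome. That is plausible, and a planned analysis of six area values is not established. But the words that define the primary test still conflict with the outcome sections, and the defence supports replacing them.

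A reader might infer three stronger things that the documents do not support.

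- **That the ratio cannot be obtained.** The volunteer lists hold newborn and immunization information, and the fuller protocol is not shown. What can be said is that no outcome source is named.
- **That a 10-point rise is impossible because the birth dose is near its ceiling.** The Introduction gives "98% for the Bacille Calmette Guerin (BCG) vaccine", but this is national coverage and is not given as coverage at birth. The article says only that "the first vaccine (BCG) is often administered immediately after birth", that 43% of children receive vaccines at the scheduled ages, and nowhere that this vaccine is the one meant.
- **That average district density implies only a handful of catchment births.** Table 2 plans 150 women per arm with a child under 1 year within 1 km. That suggests about 150 × 8/12 = 100 births per arm in eight months, so the average is a poor guide to these sites.

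The 26% and 17% figures are also conditional: they hold only if newborn means a child born after baseline to a panel member.

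**Conclusion.** The point stands as a contradiction within the article, not as detail left to an analysis plan. The primary hypothesis names a catchment ratio, the primary outcomes are individual survey measures, and no described outcome source yields the ratio.

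Read from the panel as post-baseline births, the hypothesis has about 26% power (normal) or 17% (t, 4 df). Read as the survey behavior outcome, it has about 72% or 49%. The shortfall from 80% arises because the 380 per arm includes pregnant women and prospective mothers, who give intent only.

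These figures rest on the plan's 83%, 93%, ICC 0.01 and 20% attrition, and on a two-sided test, equal cluster sizes and a comparison of end-line proportions without baseline adjustment. The t column lowers every row, including the plan's own, so rows should be compared within a column. The contradiction itself depends on none of these assumptions.

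**What to change.** In the Quantitative analysis section, replace the birth ratio with one primary outcome among mothers of children under 2: the index child has, or has not, received every National Immunization Schedule dose due by its age at interview. Analyse it with children clustered in the six catchment areas. Report intent separately in the cohorts that answer it. If a catchment rate from registers or volunteer lists is wanted, make it secondary and name its source and its numerator and denominator.

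Restate power for this outcome: 240 per arm after attrition, about 72% (normal) or 49% (t, 4 df), in place of 80%. Make the change before end-line data are seen.

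The survey already has items on adherence to the schedule, so the change is mainly to text. It has three costs. The stated power becomes less favourable, and intent loses its co-primary status. The schedule is also complete by 15 months, so children already past that age at baseline can change status only through catch-up doses, which limits how much of the 1–2 year cohort can respond. The power statement should acknowledge this.

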### Study design

We will use a clustered quasi-experimental design with panel data to measure the impact of the intervention on immunization behaviors, intent to vaccinate, and uptake of other health services. Participants from each of the six study sites will complete a baseline survey preceding intervention implementation and an end-line survey approximately eight months later. Data collectors will read questions aloud to participants and then record responses on a handheld tablet. Surveys are available as
*Extended data* (
[name], 2020).

In addition, the physical conditions of the health facilities and immunization centers will be assessed using checklists at baseline. These checklists will be used to corroborate subjective reports from interviews, focus group discussions, and surveys and assist with identifying needed resources to include in the intervention design. Our data collectors will visit each health facility and the surrounding immunization centers on the designated “Immunization Day” to complete the checklists.

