### Sampling

Like the qualitative methods, FCHVs from each ward will assist in identifying women in the community who fit the eligibility requirements. With their list of names and locations, data collectors will randomly select houses for recruitment. The target sample size is
*n* = 950 (treatment = 475, control = 475) with an anticipated attrition rate of 20%. This was determined by assuming an increase in vaccination rates from 83% (2019 estimate) to 93% (envisioned), an alpha level of 0.05 and power of 80%, and data collection from 6 clusters. To estimate the vaccination rate in Makwanpur in 2019, we assumed an increase of approximately 6% from 2017, when the data were last reported, based on antigen coverage trends from 2014 to 2017 (
Ministry of Health Nepal Department of Health Services, 2018). We estimate an intraclass correlation of 0.01, making the required sample size 380 in the treatment and 380 in the control groups. However, because this is a panel design, we envision an attrition rate of 20%, which brings our sample size at baseline to 950. We will sample four cohorts of women with children younger than one year, women with children between 1–2 years, women who are pregnant at baseline, and prospective mothers. We anticipate greatest availability of women in the first two cohorts, and the least availability of pregnant women, which we expect will create variation in our sample sizes between cohorts. For the complete anticipated sampling breakdown, see
Table 2.

**Table 2. T2:** Breakdown of quantitative data collection by treatment and control facilities.

Participant	Control	Treatment	Total
Women with children <1 year	150	150	300
Women with children 1–2 years	150	150	300
Pregnant women	50	50	100
Prospective mothers	125	125	250
Total	475	475	950

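### The primary outcome is written as a catchment-level rate over all live births, while the hierarchical model, the surveys and the sample size all take the individual woman or child as the unit

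*Protocol article*

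**What the plan says.** In the protocol article, Data analysis, Quantitative, three consecutive sentences define the primary test.

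- The objective concerns "greater vaccination uptake (or intentions for vaccination) among mothers (or prospective mothers) in the treatment, compared to the control, arm". The unit here is the woman.
- The model and the tested quantity follow: "Hierarchical linear regressions (HLM) will be used to test the primary hypothesis" about "vaccination rates (number of newborns vaccinated divided by total live births within a catchment area". The unit here is the catchment, and the denominator is every live birth in it.
- Then: "This analysis will take into account the clustered nature of data within each of the six catchment areas", three in each arm. This presupposes several observations per catchment.

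Under Quantitative methods, the other sections stay with individuals.

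- Study design: "We will use a clustered quasi-experimental design with panel data to measure the impact of the intervention on immunization behaviors", with surveys at baseline and about eight months later.
- Instruments: "Baseline and end-line surveys will measure primary outcomes of immunization behavior and intent to immunize future children". Mothers of children under 2 receive the behaviour items. Pregnant women and prospective mothers receive intention items instead.
- Sampling: the calculation rests on "assuming an increase in vaccination rates from 83% (2019 estimate) to 93% (envisioned"), alpha 0.05, 80% power, six clusters and an ICC of 0.01, "making the required sample size 380 in the treatment and 380 in the control groups". Attrition of 20% raises this to 475 per arm. Table 2 allots 300 per arm to mothers of children under 2.

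**The concern.** A hierarchical model with catchment as the upper level needs lower-level observations inside each catchment. A vaccinated-over-live-births ratio supplies one number per catchment and per time point. Its denominator is also not the surveyed sample, so the recruited women are not the units of the rate as written. The sample size has meaning only if individuals are the lower-level units.

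Two analysts following this section could therefore run different primary tests, with different units, denominators, degrees of freedom and power. This is a stated definition that does not fit the design. It is not a detail left to a fuller document.

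**Working it through.** **Inputs.** From Sampling: p1 = 0.83, p2 = 0.93, alpha 0.05 (taken as two-sided, which fits the stated figure better than one-sided), power 80%, ICC 0.01, six clusters, 380 per arm, 20% attrition. From Table 2: 150 + 150 = 300 mothers of children under 2 per arm. From Data analysis: three catchments per arm.

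**1. Reproduce the plan's figure.** For two independent proportions with mean 0.88:

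n = [1.96·√(2·0.88·0.12) + 0.842·√(0.83·0.17 + 0.93·0.07)]² / 0.10² = (0.901 + 0.382)² / 0.01 ≈ 165 per arm.

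Design effect with 380/3 = 126.7 per cluster: 1 + (126.7 − 1)·0.01 = 2.257. Then 165 × 2.257 ≈ 372, close to the stated 380. Power at 380 is 80.9% (effective n = 380/2.257 = 168.4). Attrition: 380/0.8 = 475, exactly as stated. The calculation is therefore an individual-level one with a design effect and normal critical values.

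**2. The model on one rate per catchment.** With a random catchment intercept (variance τ²) and a residual (variance σ²), six single observations have covariance (τ² + σ²)·I. Only the sum enters the likelihood. On six illustrative rates, the splits (τ², σ²) = (0, 0.001), (0.0005, 0.0005) and (0.0009, 0.0001) all give a log-likelihood of 13.9096. The two components cannot be separated. Their sum, and so the arm difference and its standard error, can be estimated, on 6 − 2 = 4 degrees of freedom.

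**3. Power of that 3-versus-3 comparison.** The variance of one rate is p(1−p)·[1 + (m−1)·0.01]/m, with m observations per catchment. Assume m = 126.7, i.e. 380 per arm.

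- At 0.83: 0.1411 × 2.257/126.7 = 0.002514.
- At 0.93: 0.0651 × 2.257/126.7 = 0.001160.
- SE of the difference: √[(0.002514 + 0.001160)/3] = 0.0350.
- Noncentrality: 0.10/0.0350 = 2.858; critical t on 4 df: 2.776.
- Power (noncentral t): about 58%. The normal approximation with the same SE gives 81.5%.

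The protocol does not give the number of live births per catchment, so m is an assumption. With 760 per arm, m = 253.3, SE = 0.0309 and power is about 68%. As m grows without limit, SE → √[(0.1411 + 0.0651)·0.01/3] = 0.0262 and power reaches at most about 81%.

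**4. Power of the individual analysis on those with a behaviour outcome.** 300 × 0.8 = 240 per arm, m = 80, design effect 1 + 79 × 0.01 = 1.79.

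- Effective n = 240/1.79 = 134.1; normal-approximation power is 71.4%.
- With unpooled cluster-level variances, SE = 0.0392 and noncentrality = 2.550. Power is 72.2% by normal approximation and about 49% on 4 df.

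**The case against.** The best defence is that the parenthesis is a loose gloss on the word rates. The sentence before it places uptake among mothers, the sentence after it speaks of data within catchments, and the surveys and sample size concern individuals. On that view no six-value analysis is fixed. That stands as evidence of intent, and it makes this a contradiction in the primary outcome definition. It does not remove the contradiction: the only explicit definition of the tested quantity is the catchment ratio, and its denominator differs from the surveyed population.

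The panel is a second defence. Rates formed at both waves would give 12 values, two per catchment, and a random catchment intercept would then be identifiable. This too is correct, although the Quantitative section does not say that it is planned. Comparing changes between arms would still be three against three on 4 df.

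Third, the level-1 variable, link and covariates may properly be left to an analysis plan. That is fair, and no fault is found in their absence.

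A reader might infer three stronger things, none of which the documents support.

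- **That the primary model cannot be identified at all.** Even with six values only the variance split is lost; the arm effect remains estimable.
- **That the recruited women play no part.** This holds only if the survey, sample-size and objective statements are all ignored.
- **That the standard error would be about five times too small.** On six invented rates (0.90, 0.95, 0.93 against 0.82, 0.86, 0.80) one optimiser (L-BFGS) does return 0.0045, with a Hessian warning. Another (Nelder-Mead), on the same model and data, returns 0.0229, equal to the ordinary 3-versus-3 value. The factor is a numerical artefact.

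**Conclusion.** The point holds as an inconsistency in the unit, numerator and denominator of the primary outcome. The written ratio fits neither the hierarchical model beside it, nor the survey-measured outcomes, nor the individual-level sample size.

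The inconsistency matters because the planned 80% depends on the unit chosen. A 3-versus-3 test of ward rates has about 58% power at 380 per arm. An individual analysis restricted to mothers of children under 2 has roughly 71–72% by normal approximation and about 49% on 4 df.

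These figures assume an ICC of 0.01, equal cluster sizes, a two-sided 5% test, a ten-point difference, no gain from baseline adjustment and no use of the matching within Palikas. The 58% also assumes 380 observations per arm behind the rates. More births behind each rate would raise it, to no more than about 81%.

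**What to change.** Choose one unit in Data analysis, Quantitative, and make the outcome definition follow it.

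- **Preferred:** replace the parenthetical ratio so that the dependent variable is each surveyed child's vaccination status (yes/no) among mothers of children under 2, with children nested in the six catchments and arm as a catchment-level predictor. Test arm on small-sample degrees of freedom (about 4). Report ward rates descriptively.
- **Alternative:** if the ward rate over live births is kept, drop the hierarchical model and state a 3-versus-3 cluster-level comparison. Name the source of the live-birth counts.

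In either case, restate the power in Sampling for the chosen unit. Rewording alone does not restore agreement with 380 per arm, because only about 240 per arm will have a behaviour outcome after attrition.

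The cost is wording plus a power recalculation. The preferred option needs no new data. The article reports that baseline collection is complete, so any shortfall in power would have to be acknowledged or met through the analysis.
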